### Patient-reported outcomes

Patients will be asked to complete quality of life questionnaires (QLQ-C30 and QLQ-BR23) [38] at four key time points: upon study enrollment, on the day of RT treatment, 2 weeks postsurgery, and at the 12-month follow-up. Additionally, patient-based cosmetic evaluations will also be reported on the questionnaires.

### Sample size

Based on the eligibility criteria, 30 patients are expected to provide consent and be recruited over the 2-year study period. This number of patients will provide an estimated 95% confidence limit of feasibility consisting of a lower bound of 74.4% and an upper bound of 96.5% (based on the Wilson score interval approximation), if a feasibility proportion of 90% is achieved.

### Statistical methods

Descriptive summary statistics will be determined to summarize the patient clinical characteristics, responses to patient-reported outcome questionnaires, and rates of adverse events at each follow-up time point. The primary outcome will be reported as the proportion of patients who can be feasibly treated with MRI linac using a single-fraction APBI technique. The denominator includes all patients who met the study eligibility criteria and provided consent to participate. Success for this outcome will be defined as achieving this treatment outcome in at least 90% of patients. For the secondary outcome assessment, univariate analysis will be performed to investigate the association between MRI parameters and the tumor response rate. Categorical variables (i.e., Clavien–Dindo grade) will be presented as counts and percentage frequencies, while continuous variables (i.e., quality of life or patient-reported outcome measures) will be presented as the mean ± standard deviation if they are normally distributed or the median (interquartile range) if their distribution is skewed.

Pearson or Spearman’s rank correlation coefficients will be used to assess correlations for normally and non-normally distributed continuous variables, respectively. Appropriate parametric or nonparametric tests will be applied to assess associations between the MRI data and histopathological features of the patients. Additionally, the MRI results will be compared between good responders to treatment and poor responders to treatment. Receiver operating characteristic (ROC) curve analysis may be employed to determine cut-off points for evaluating associations between continuous variables and binary outcomes, such as the tumor response rate.

All the statistical analyses will be conducted using Stata version 18.0 (StataCorp, College Station, Texas, USA). A *p*-value of less than 0.05 will be used to indicate statistical significance. However, we recognize that the study may be underpowered to detect statistical significance for some tests of association when assessing the secondary outcomes due to the limited sample size. Given the exploratory nature of the analysis for the secondary outcomes, it is challenging to determine the number of statistical tests that will be conducted a priori. Therefore, we will focus on the magnitude of effect sizes and confidence intervals when reporting and describing the results for the secondary outcomes. This approach is likely to inform sample size calculations for subsequent fully powered trials.

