### Breast-conserving surgery

Six weeks after completing RT treatment, the patients will undergo breast conservation surgery, which consists of wide local excision for removing the tumor, along with sentinel lymph node biopsy to assess for the potential spread of cancer to the lymph nodes. In cases where the sentinel lymph node is found to be positive, indicating potential cancer spread, patients will be counseled regarding the possibility of axillary clearance. The decision for this additional procedure will be made based on the discretion of the treating surgeon, considering the individual patient's condition and treatment needs.

Histopathological assessment of the excised tissue will be performed by a pathologist with a sub-specialization in breast cancer. Tumor cells will be evaluated using hematoxylin and eosin staining and cytokeratin antibody activity. The response to treatment will be graded using the Miller and Payne Reporting Criteria [36].

Tumor samples will be securely stored within the Pathology Health biobank, and blood samples will be stored in the pathology freezer.

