### Follow-up

Several clinical assessments, cosmetic photographs, and formal acute toxicity scoring will be conducted by the treating Radiation Oncologist at key time points throughout the study. A baseline assessment will be performed prior to the commencement of treatment; then, follow-up assessments will be performed at 2 weeks, 6 months, and 12 months post-treatment.

The acute toxicity and cosmetic outcome scores will adhere to the standards set by the Common Terminology Criteria for Adverse Events (CTCAE) Version 5.0 [37].

All adverse events resulting from RT experienced by the participants will be documented in the case report form. Importantly, adverse events that could be influenced by the study interventions will be considered outcomes of the study.

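### Adverse-event rates by visit cannot show how many patients were ever harmed or how severely; a per-patient worst-grade summary should be added (minor)

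*Protocol article*

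**What the plan says.** The Statistical methods section lists, among its descriptive summaries, "rates of adverse events at each follow-up time point". It adds that categorical variables "will be presented as counts and percentage frequencies", with Clavien–Dindo grade as the example. That general rule names neither a counting period nor a counting unit.

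The Follow-up section sets a baseline assessment and says that "follow-up assessments will be performed at 2 weeks, 6 months, and 12 months post-treatment". It also states that "formal acute toxicity scoring will be conducted by the treating Radiation Oncologist at key time points throughout the study", using "Common Terminology Criteria for Adverse Events (CTCAE) Version 5.0".

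Recording is broader than the visit schedule. The same section says that "All adverse events resulting from RT experienced by the participants will be documented in the case report form", and that "adverse events that could be influenced by the study interventions will be considered outcomes of the study".

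The Breast-conserving surgery section places the operation between the first two post-treatment visits: "Six weeks after completing RT treatment, the patients will undergo breast conservation surgery".

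**The concern.** What is collected and what is reported do not match. Collection covers every radiotherapy-related event, and events that the interventions could influence have the status of outcomes. The one stated adverse-event summary, however, is organised by visit. It does not say whether a rate means events present on the day or events since the previous visit, or whether the numerator counts events or patients.

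In a 30-patient study of a single ablative fraction, a reader mainly wants to know how many patients had any toxicity, how many reached grade 2 or higher, and how many reached grade 3 or higher. Visit rates cannot answer that, because they do not show whether the same or different patients are affected from one visit to the next.

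The schedule adds to this. The 2-week and 6-month visits are about 24 weeks apart and surgery falls in that gap. The Follow-up section lists no toxicity assessment between week 2 and surgery, so toxicity from radiotherapy alone is not separated from what follows the operation, except at week 2.

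**Working it through.** **Inputs.** From the article: 30 patients (Sample size); post-treatment visits at 2 weeks, 6 months and 12 months (Follow-up), taken as weeks 2, 26 and 52; surgery at week 6 (Breast-conserving surgery). The article gives no toxicity rate, so the rates, durations and onset pattern below are assumptions for illustration.

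**The plan's own figure.** The only computed design figure is the Wilson interval for 90% feasibility. For 27/30 with z = 1.96:
- centre = (0.9 + 3.8415/60) / (1 + 3.8415/30) = 0.8546
- half-width = 1.96 × √(0.9 × 0.1/30 + 3.8415/3600) / 1.1280 = 0.1108

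This gives 74.4% to 96.5%, as stated. The present point does not depend on it.

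**Step 1: what visit rates say about patients ever affected.** Suppose k of 30 patients have an event counted at each of the three visits. If they are the same patients each time, k/30 are affected. If they are different patients, 3k/30 are.

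| k per visit | Visit rate | Fewest patients affected | Most patients affected |
|---|---|---|---|
| 3 | 10% | 3/30 = 10% | 9/30 = 30% |
| 6 | 20% | 6/30 = 20% | 18/30 = 60% |

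If rates cover the time since the last visit, these limits apply to all recorded events. If rates cover only events present at the visit, the limits apply only to patients seen with an event, and the true share can be higher. Worst grade is equally undetermined.

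**Step 2: what is lost if only events present at the visit count.** The gap between the first two visits is 26 − 2 = 24 weeks. Let an event last D weeks (D from 2 to 12), with onset uniform over 52 weeks (assumption). It is present at week 2 only if it began in weeks 0 to 2, at week 26 only if it began in the preceding D weeks, and likewise at week 52. The chance of being present at some visit is therefore (2 + D + D)/52.

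| Duration D | Present at some visit | Present at no visit |
|---|---|---|
| 2 weeks | 6/52 = 12% | 88% |
| 4 weeks | 10/52 = 19% | 81% |
| 8 weeks | 18/52 = 35% | 65% |
| 12 weeks | 26/52 = 50% | 50% |

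If 6 of 30 patients (20%) each had one 8-week event, 6 × 18/52 = 2.1 would be seen at any visit, about 7% of 30. If rates cover the interval since the last visit, none of these recorded events is lost and Step 2 falls away. Step 1 does not.

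**Step 3: precision of a per-patient figure.** Exact two-sided 95% upper limits, if all 30 are treated:
- 0/30: 1 − 0.025^(1/30) = 11.6%
- 1/30: the p that solves (1 − p)^30 + 30p(1 − p)^29 = 0.025, which is 17.2%

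No severe events in 30 patients would thus still be compatible with a true rate above 10%.

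**The case against.** The strongest reply is that the text never says the rates are point prevalence. Because all radiotherapy-related events go into the case report form, a rate may well cover the interval since the last visit. That is a fair reading. A reader might infer that an event starting and resolving between visits is counted nowhere, but the document does not support this: the event is recorded, and on the interval reading it appears at the next visit.

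A reader might also infer that lasting events are counted several times. Appearing in several visit tables is normal for visit-wise reporting. It becomes double counting only if visits are added, which the article does not plan.

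A further reply is that this is a condensed article, and a cumulative table may be in the full protocol or analysis plan. That also stands, so it cannot be said that the trial will not report one. Nor can it be said flatly that no interval is planned. The article promises to emphasise confidence intervals for secondary outcomes, although it names only the relationship between MRI and histopathology as the secondary objective, so coverage of toxicity is unclear.

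What survives is narrower. The article does name a toxicity summary, leaves its period and unit undefined, and on neither reading does that summary yield the per-patient figure.

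**Conclusion.** The point holds as a minor improvement. Visit rates as stated do not identify the proportion of patients ever affected or their worst grade, whichever way they are read: 10% at each visit fits 10% to 30% of patients. This follows from the form of the summary and needs no assumption about onset or duration.

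The loss of transient events (about 65% for 8-week events) is conditional. It requires the present-at-visit reading and uniform onset over 52 weeks. The article supports neither in particular, and if onset clusters at other times the share changes. It shows why the wording should be settled and is not an estimate of under-reporting in this trial.

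Severity is low because toxicity is descriptive, feasibility is the primary endpoint, and the required recording is already planned.

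**What to change.** In the Statistical methods section, add wording along these lines:

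*From all events documented in the case report form, each patient's worst CTCAE grade will be derived for the period from RT to surgery and from RT to 12 months. The number and proportion of patients with any, grade 2+ and grade 3+ events will be reported with exact 95% confidence intervals. Rates by visit will be supplementary, with their counting period and unit stated.*

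The cost is one extra table and a headline rate that is likely to look less favourable than the visit rates. No further visit or patient is needed. The split at surgery assumes that the case report form holds onset dates, which should be confirmed.

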## Discussion

In the RICE trial, we will administer a single fraction of preoperative APBI using the MRgRT on an MRI linac, with the hypothesis that enhanced treatment accuracy and acceptable post-surgical breast cosmesis can be achieved. The MRI linac system’s ability to integrate real-time MRI with a RT treatment machine offers superior tumor-targeting precision over traditional CT-Linac external beam methods. This precise targeting allows accurate tumor radiation while protecting surrounding healthy tissue. Additionally, the single-fraction approach is expected to enhance patient experience and convenience, potentially reducing hospital visits and streamlining treatment.

The optimal dose and timing for removing an irradiated tumor remain debated, with various prospective trials exploring a variety of options, including treatment technique and dose. In our study, we will administer a single 21-Gy fraction, with pathological response assessment planned for 6 weeks after treatment. Given the exploratory nature of this study, our decision to use this dose was based on prior studies [5, 28–30] that have demonstrated its effectiveness without significant RT-related side effects and improved overall quality of life. Given the variability among studies investigating single-fraction APBI [4–6, 28–30], particularly in terms of the time intervals and techniques used, it is anticipated that a portion of patients will demonstrate a response to treatment. Nevertheless, since no study to date has explored, the response to treatment 6 weeks after single-fraction preoperative RT using the MRI linac, these outcomes remain largely unexplored.

Currently, RT schedules are typically uniform across patients’ treatments, despite the variability in treatment response among individuals. Some patients exhibit significant tumor residue post-treatment, while others achieve a near-complete pathologic response. If imaging can accurately differentiate between responders and non-responders before or after RT, it may be possible to tailor treatment more precisely. For potential responders, dose de-escalation could reduce treatment toxicity while maintaining favorable oncological outcomes. Conversely, poor responders might benefit from a more aggressive treatment plan.

In our study, we intend to collect MRI data both before and after treatment to correlate these parameters with radiation response biomarkers. This method aims to explore the potential of MRI as a non-invasive tool for assessing treatment efficacy. Additionally, our study includes baseline [18F] FDG-PET-CT and [18F] FES-PET-CT to determine whether pre-treatment molecular imaging can identify potential RT responders before intervention. Given our inclusion criteria for the RICE trial — ER + sub-type tumors smaller than 2 cm — we have specifically chosen to evaluate the use of [18F] FES-PET-CT. This decision aims to determine whether this radiotracer offers greater sensitivity and specificity compared to the standard [18F] FDG-PET-CT, particularly given the limitations of [18F] FDG-PET-CT in detecting small tumors and its variable sensitivity in ER + sub-types which have low glucose uptake [39–41]. We anticipate that [18F] FES-PET-CT, an ER-sensitive radiotracer, will improve the detection of such lesions and enhance the diagnostic workup for RT planning and treatment.

## Conclusions

In conclusion, the RICE trial is a single-institution prospective study that will contribute to the growing literature on the use of single-fraction preoperative RT in early-stage breast cancer patients. This trial primarily focuses on the feasibility of MRgRT as a novel treatment tool that could potentially represent a significant advancement in early-stage breast cancer treatment and clinical research. The insights and experiences gained from this trial are expected to inform and enhance future research in this area, ultimately leading to improved patient outcomes and care.

## Data Availability

Data and materials will not be made available until the end of the study and upon request.

## Abbreviations

MRgRT: Magnetic resonance imaging-guided single-fraction pre-operative radiotherapy
RICE Trial: Magnetic Resonance Imaging-Guided Single-fraction Preoperative Radiotherapy for Early-Stage Breast Cancer
MRI: Magnetic resonance imaging
WLE: Wide local excision
APBI: Accelerated partial-breast irradiation
MRI linac: Magnetic resonance imaging linear accelerator
18F-FDG PET/CT: [18F] fluorodeoxyglucose positron emission tomography
ER +: Estrogen receptor-positive
PR +: Progesterone receptor-positive
HER2 +: Human epidermal growth factor receptor 2 positive
PTV: Planning target volume
CTV: Clinical target volume
GTV: Gross target volume
CT: Computed tomography
DCE-MRI: Dynamic contrast-enhanced magnetic resonance imaging
CTCAE: Common Terminology Criteria for Adverse Events
Gy: Gray
HREC: Human Research Ethics Committee
PPV: Positive predictive value
NPV: Negative predictive value
RT: Radiotherapy
